Pulsed field ablation (PFA) is primarily a nonthermal ablation technique that causes cell death by creating pores in myocyte membranes.^21^^,^^22^ Although the nominal dimensions of the myocardial PFA lesions may be comparable with RFA, the former may be more efficient and consistent in creating lesions in scarred substrate.^23^, ^24^, ^25^ Just as importantly, in contrast to RFA, PFA lesions can be created much more rapidly (typically <10 seconds per site) and with the use of minimal or no irrigation. In contrast, the use of PFA may be associated with an increased risk of certain adverse events that are relatively specific to this technology; as shown in ablation studies targeting atrial arrhythmias, this includes the risk of coronary vasospasm and hemolysis-related acute kidney injury.^26^^,^^27^ Even so, the recently published aggregate ADVANTAGE AF data suggest that the overall safety profile for atrial PFA ablations is very favorable (primary safety endpoint rate 2.0%; myocardial infarction rate 0.2%; and clinically relevant hemolysis rate 0.6%, although no events required hemodialysis).^28^

Several small studies and case reports have examined the safety and efficacy of PFA in the context of VT ablation.^29^, ^30^, ^31^, ^32^, ^33^, ^34^ Larger cohort data on PFA ablation of VT and premature ventricular contractions have only been published recently. This includes our own experience with a large-footprint pentaspline PFA catheter (n = 11)^35^ and a larger series by Ruwald et al^36^ (n = 35) that relied on a focal ablation catheter and PFA generator. The outcomes in VT ablation were similar to what was previously reported with focal RFA catheters. In particular, Ruwald et al^36^ saw a 55% 1-year recurrence rate in VT ablation patients. However, it is important to state that the studied population was enriched for high-complexity cases with intricate, nonischemic substrate. Although the complication rates in these (and other) studies are reassuring,^35^, ^36^, ^37^ the safety of PFA is yet to be confirmed in a more uniform population.

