### Follow-up

The outline of the follow-up data collection strategy is presented in Table 2. Primary and procedural efficacy along with adverse event review will be performed immediately after the procedure and at the time of hospital discharge. Study visits 1 (7-40 days after the procedure) and 2 (90 ± 30 days after the procedure) will include functional assessment, ICD interrogation, and adverse event review. The final study visit (day 180 ± 30 after the procedure) will be a comprehensive assessment that will include transthoracic echocardiography and the 36-item short form health survey.

**Table 2 tbl2:** Schedule of activities

Procedures	Screening and enrollment/baseline, day −90 to −1	Ablation procedure	Discharge	Study visit 1, day 7–40∗	Study visit 2, day 90 ± 30∗	Final study visit, day 180 ± 30
Informed consent	X					
Demographics	X					
Medical history	X					
Physical examination	X		X			X
NYHA assessment	X			X	X	X
Vital signs	X		X			X
TTE†	X					X
ECG	X					X
ICD interrogation‡	X	X		X	X	X
SF-36	X					X
Adverse event review and evaluation		X	X	X	X	X
Complete case report forms	X	X	X	X	X	X

ECG = electrocardiogram; ICD = implantable cardioverter-defibrillator; NYHA = New York Heart Association; SF-36 = 36-item short form health survey; TTE = transthoracic echocardiogram.

∗ In-office visit or telephone/virtual visit. ICD interrogation can be monitored remotely.

† TTE at baseline to be performed within 6 months of enrollment.

‡ ICD interrogation can be performed via remote monitoring.

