### Statistical analysis and power calculations

The primary null hypothesis is that the total ablation time needed for complete LAVA elimination (ie, primary efficacy metric) will not be different between the 2 study arms. This hypothesis will be tested using a 2-sample *t* test.

PFA lesion delivery time will be, by design, shorter (3 2.5-second pulse trains = 7.5 seconds per ablation site) than RFA (at least 30 seconds per lesion). Furthermore, effective RFA lesion dimensions may vary widely depending on the distribution of myocardial scar, whereas PFA lesions are expected to be more consistent.^25^^,^^38^ Therefore, we envisage the time needed to eliminate targeted LAVAs to differ by at least 50% between the 2 study arms. With a desired power of 80% and a significance level of 0.05, the predicted minimum enrollment is 36 patients (18 in each study arm). This will be increased to 40 patients to allow for a 10% withdrawal rate. 10 additional patients will be screened to allow for possible screen failures.

The secondary efficacy and both primary and secondary safety endpoints will be analyzed using *t* test, rank sum test, or Fisher’s exact test, as appropriate. Time-dependent outcomes will be analyzed as landmark events. However, if the event rates and/or dropout rates are high in either group (≥20%), time-to-event methodology will be adopted (Cox regression and Fine-Gray competing risk models, as appropriate). Univariate and multivariable models will be used.

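### A 20% event or dropout rate in either arm (4 of 20 patients) decides whether time-dependent secondary outcomes are summarised as a 6-month proportion or a hazard ratio

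*Protocol article*

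**What the plan says.** All of this is in the protocol article, mostly in the section on statistical analysis and power calculations.

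- The default: "Time-dependent outcomes will be analyzed as landmark events". Table 3 sets the assessment at 6 months, so I read this as event status, and hence a proportion, at 6 months.
- The exception: "if the event rates and/or dropout rates are high in either group (≥20%), time-to-event methodology will be adopted".
- The methods after the switch: "Cox regression and Fine-Gray competing risk models, as appropriate". The next sentence adds "Univariate and multivariable models will be used".
- Otherwise, secondary efficacy and safety endpoints "will be analyzed using *t* test, rank sum test, or Fisher’s exact test, as appropriate".

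The trial design section gives 40 patients randomized 1:1. Table 3 lists five time-dependent secondary endpoints: VT recurrence with appropriate ICD intervention or symptoms, sustained VT below the ICD detection rate, all-cause mortality, VT burden before and after ablation, and cardiovascular admission. The table and the limitations paragraph both state that the trial is not powered for these outcomes.

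**The concern.** A rate in either group is an outcome or dropout rate split by arm, and it is known only once follow-up has accumulated. The results therefore select the analysis. More than the test changes: one branch gives a 6-month proportion, the other a hazard ratio or a subdistribution hazard ratio. These answer different questions and cannot be exchanged when planning a later trial.

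The Discussion says the trial should supply early information for designing a large comparative trial. That calls for an effect measure known in advance. As the rule stands, one patient more or less in one arm can change what is estimated. Below the trigger, a simple landmark proportion has no means of using the time that withdrawn patients did contribute.

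**Working it through.** **Inputs.** From the article: at least 36 patients, a 10% withdrawal allowance, 1:1 allocation, a 20% threshold in either arm. The article gives no expected 6-month event rates for this trial, so true rates are assumed and shown over a range.

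**The plan's own figure.** 36 / (1 − 0.10) = 40, as stated, hence 20 per arm.

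**Size of the trigger.** 0.20 × 20 = 4 patients. With 18 per arm, 0.20 × 18 = 3.6, so again 4.

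**Chance that events alone fire it in at least one arm**, with the same true rate p in both arms: 1 − [P(X ≤ 3)]², X ~ Binomial(n, p). For n = 20 and p = 0.10, P(X ≥ 4) = 0.133 in one arm, so 1 − 0.867² = 0.248.

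| Assumed true rate | 20 per arm | 18 per arm |
|---|---|---|
| 5% | 3% | 2% |
| 10% | 25% | 19% |
| 15% | 58% | 48% |
| 20% | 83% | 75% |
| 25% | 95% | 91% |
| 33% | 99.6% | 98.9% |

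**Dropout alone.** Applying the 10% withdrawal allowance to each patient over 6 months gives the same calculation: 25% with 20 per arm.

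**Both routes.** At a 10% event rate and 10% withdrawal, treated as independent: 1 − (1 − 0.248)² = 0.43. A simulation in which an event and a withdrawal compete within a patient gave 40%.

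**VT recurrence.** The only recurrence rate in the article is from an earlier series of more complex cases that "saw a 55% 1-year recurrence rate in VT ablation patients". Under a constant hazard, the 6-month rate is 1 − 0.45^0.5 = 0.33. The switch is then almost certain, and the stated default would hardly ever apply to this endpoint.

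**Type I error.** I simulated 4,000 trials per scenario with 20 per arm, exponential event times and 10% withdrawal. The landmark test was Fisher's exact test with withdrawn patients counted as event-free; the log-rank test stood in for Cox.

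| True rate, both arms | Always Fisher | Always log-rank | Switching rule |
|---|---|---|---|
| 10% | 0.9% | 3.2% | 3.2% |
| 15% | 1.6% | 4.5% | 4.5% |
| 20% | 1.9% | 4.7% | 4.7% |
| 33% | 2.4% | 4.7% | 4.7% |
| 50% | 2.0% | 5.4% | 5.4% |

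The simulation standard error at 5% is √(0.05 × 0.95 / 4000) = 0.34 percentage points, so 5.4% is compatible with 5%.

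**Partial follow-up below the trigger.** Up to 3 of 20 (15%) may be lost in an arm; 0.10 × 20 = 2 are expected. Suppose 3 patients have events and 3 others are lost. The proportion is 3/20 = 15.0% if the lost count as event-free, 3/17 = 17.6% if they are excluded, and 6/20 = 30.0% if all had events. A Kaplan-Meier estimate lies between the first two, according to when the losses occurred.

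**Sparse data.** A 4 versus 0 split fires the trigger, yet with no events in one arm the Cox hazard ratio has no finite estimate (Fisher p = 0.106). Because dropout is a separate trigger, 4 withdrawals in an arm call for regression models however few events there are.

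**The case against.** The best defence is that the threshold is numeric and stated beforehand, so the trigger itself leaves the analyst no discretion, and that it does no harm to testing. Both parts stand. Below the trigger the most extreme split is 3 versus 0 of 20, which neither Fisher's test (p = 0.23) nor the log-rank test (p about 0.08) calls significant. That is why the rule rejects as often as always using the log-rank test. A reader might infer inflated type I error from a data-dependent choice of method; the calculation does not support that for a single unadjusted comparison. It did not cover the choice between Cox and Fine-Gray or the multivariable models.

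Other stronger readings also fail:

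- *Time-to-event regression suits any event rate, so a trigger has no purpose.* With 20 per arm, the chance that at least one arm has no events is 1 − (1 − 0.95^20)² = 59% at a true rate of 5%, and 23% at 10%. Keeping hazard ratios for commoner events is a sensible aim. This trigger just does not achieve it.
- *The landmark analysis ignores death as a competing event.* With complete follow-up, the crude 6-month proportion with VT equals the cumulative incidence with death competing. Only dropout separates them.
- *Withdrawn patients will be discarded or counted as event-free, or different endpoints will get different methods.* The article says neither. It leaves open how the landmark analysis treats dropouts and whether the trigger works per endpoint or across all of them; a full analysis plan may settle both.
- *The visit window spoils the comparison.* The article does say "The final study visit (day 180 ± 30 after the procedure", but Table 3 assesses these outcomes at 6 months and ICD interrogation may be remote, so dated events can be cut at day 180.

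Finally, VT recurrence would probably be analysed by time-to-event methods anyway, which narrows the practical effect to the less frequent endpoints.

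**Conclusion.** The point holds as a minor one. The published text lets 4 patients in one arm decide whether the treatment effect is a difference in 6-month proportions or a hazard ratio. For true event rates of roughly 10% to 20%, chance has a large say in which it is. The loss is a stable effect measure and the use of partial follow-up from the 2 or so patients per arm expected to withdraw. In the worked example, excluding the lost patients or counting them as event-free shifts the estimate by 2.6 percentage points at most from Kaplan-Meier.

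The probabilities rest on assumed event rates, equal in both arms, on independence between patients, and on reading the withdrawal allowance as a 6-month loss rate. The primary endpoint, ablation time compared by a t test, is untouched. The affected endpoints are secondary and declared unpowered.

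**What to change.** Delete the 20% trigger and fix one method per endpoint in advance:

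- all-cause mortality: Kaplan-Meier;
- VT recurrence (both definitions in Table 3) and first cardiovascular admission: cumulative incidence with death as a competing event;
- for each of these, count events to day 180 and report the 6-month estimate with 95% CI per arm, and the difference between arms;
- Cox or Fine-Gray hazard ratios as supportive results only, and only where both arms have events;
- VT burden: a separate analysis as a count, since time-to-event methods do not fit a before-and-after number of therapies.

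The cost is wording and slightly more analysis work. ICD interrogation and adverse event review at each follow-up visit should already supply event dates. The downside is that hazard ratios will be absent or imprecise for rare endpoints.

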## Discussion

The ASCEND-VT pilot trial is the first randomized prospective study designed to assess the procedural efficacy and safety of VT ablation in patients with ICM, using a focal PFA catheter vs standard RFA technology. The primary efficacy metric of ASCEND-VT is intended to directly compare PFA vs RFA with respect to the time that it takes to eliminate abnormal endocardial potentials (specifically, LAVAs) in this population.

This study design was chosen to test the anticipated primary advantage of the PFA technology in this context: its expected ability to achieve the same procedural endpoint as standard ablation but in a more streamlined fashion. If the ASCEND-VT study reveals similar ablation times between PFA and RFA along with comparable safety profiles, then that alone may boost the former technology’s clinical appeal given that the PFA apparatus does not require large volumes of open irrigation. Furthermore, if the ASCEND-VT study reveals a large primary effect size (ie, large difference in ablation times between the 2 study arms), then we may even postulate a trend toward procedural “superiority” of PFA, that is, substantially shorter ablation that can translate into shorter procedural times, which will confer additional benefits on the patients such as shorter exposure to anesthetic agents, less time under positive pressure ventilation, and overall lower procedural complication risk, as previously reported.^39^

With that in mind, we expect most of the other secondary outcome metrics (such as fluid input/balance and total procedural duration) to mirror the primary outcome. In further secondary analyses, the ASCEND-VT study will also compare the numbers of cases where total elimination of LAVAs could not be achieved. As discussed earlier, this endpoint is sometimes unachievable using RFA.^15^^,^^20^ In contrast, interpretation of this finding may be challenging considering the reversible nature of PFA in certain scenarios.^40^

The ASCEND-VT study will also look at hard clinical outcomes such as VT recurrences and all-cause mortality, although the power to detect any signal in this realm may be limited. Indeed, establishing overall clinical noninferiority of 1 ablation technology over another, for example, proving that the use of PFA results in lower VT recurrence or lower mortality than RFA, will necessitate a large-scale multicenter trial with an extended follow-up time. However, ASCEND-VT will provide important early information to design a large head-to-head comparative trial.

The ASCEND-VT study is also intended to systemically assess the safety of PFA in ICM VT ablations. Although the rate of vascular or major mechanical cardiac adverse events (eg, pericardial effusion and tamponade) is expected to be comparable between the 2 study arms, certain potential complications are relatively specific to PFA and will need to be separately assessed. First, early PFA literature (particularly in the context of atrial ablation) has shown that transient hemolysis is a relatively frequent consequence of PFA ablation, although the incidence of resulting end-organ damage is very low.^28^^,^^41^^,^^42^ For this reason, the ASCEND-VT trial will specifically track the rate of acute kidney injury after the procedure. Second, PFA in the atrium may result in vasospasm when applied in the vicinity of coronary arteries^26^^,^^43^; although patients in ASCEND-VT will only be subjected to ventricular endocardial PFA applications (ie, not near the epicardial coronary vessels), the possibility of vasospasm with or without substantial myocardial injury will be closely tracked. However, the potential for vasospasm is not unique to PFA alone, having previously been demonstrated with RFA, and will be evaluated in both arms. Third, even in the absence of new coronary injury, there is a theoretical concern that the uniform and large PFA lesions may have an effect on myocardial contractility, especially if applied outside of noncontractile scar^44^; therefore, the ASCEND-VT trial will pay particular attention to any perturbations in LVEF and/or evidence of new wall motion abnormalities after ablation.

The limitations of the ASCEND-VT trial primarily stem from the study’s relatively small size. As discussed earlier, the trial is not powered to detect differences in clinical outcomes (such as VT recurrences or mortality) between the 2 study arms. Similarly, the study may not be able to estimate the relative risk of PFA for presumably uncommon complications (eg, stroke). Furthermore, the trial is not designed to confirm the durability of LAVA elimination; this may be particularly relevant in the PFA arm where local electrogram elimination may be reversible in some cases. In addition, the ASCEND-VT trial will use different mapping systems and mapping catheters in each arm—a logistical constraint stemming from each mapping system’s compatibility with the used ablation catheters. This heterogeneity in the mapping apparatus may inadvertently result in the designation of slightly different ablation targets in each study arm. An analysis will be undertaken wherein the time needed to eliminate LAVA will be normalized to the total surface area exhibiting LAVA at baseline. This additional analysis would generate results independent of the used mapping system and may be a more objective metric of substrate ablation efficiency.

Although the primary study endpoint is elimination of all LAVAs, induction and mapping of VTs when feasible are also allowed to ensure targeting more rare subtypes of non–scar-related VTs. Given the randomized nature of this study, this would not be expected to substantially affect the primary study endpoint.

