### Ablation procedure: Substrate mapping

In the control arm, the choice of mapping system and mapping catheters will depend on the operator’s discretion using a commercially available electroanatomic mapping system and mapping catheter. In the intervention arm, mapping will be done using the OPAL HDx mapping system (Boston Scientific, Marlborough, MA) along with the ORION multipolar basket catheter (Boston Scientific). Ablation catheters (outlined below) may also be used for mapping in all patients.

In both study arms, substrate mapping will be done during sinus rhythm and/or paced rhythm.

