### Ablation procedure: Definition of substrate target

The main substrate ablation target will be LAVA electrograms within the abnormal substrate. These are defined as sharp high-frequency ventricular potentials, possibly of low amplitude, distinct from the far-field ventricular electrogram occurring any time during or after the far-field ventricular electrogram in sinus/paced rhythm that sometimes display fractionation or double or multiple components separated by very-low-amplitude signals or an isoelectric interval and are poorly coupled to the rest of the myocardium.^15^ During substrate mapping, all sites with LAVAs will be marked using the mapping system. In addition, in patients with stable VTs, activation and entrainment mapping will be permitted to prioritize LAVA areas to target, whereas, in patients with unstable VTs, pace mapping from substrate areas with LAVAs will also be permitted.

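### Time per LAVA area is said to be independent of the mapping system, but this holds only if ablation time is proportional to mapped area equally in both arms' systems

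*Protocol article*

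**What the plan says.** The limitations paragraph of the Discussion states that the trial "will use different mapping systems and mapping catheters in each arm" and that this "may inadvertently result in the designation of slightly different ablation targets in each study arm". As the answer to that problem it announces an analysis in which "the time needed to eliminate LAVA will be normalized to the total surface area exhibiting LAVA at baseline". It then says of this analysis: "This additional analysis would generate results independent of the used mapping system", and suggests that it may be the more objective measure of ablation efficiency.

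The Methods show where the divisor comes from. Under Ablation procedure: Substrate mapping, "In the intervention arm, mapping will be done using the OPAL HDx mapping system", together with a named basket catheter, whereas "In the control arm, the choice of mapping system and mapping catheters will depend on the operator’s discretion". Under Ablation procedure: Definition of substrate target, "all sites with LAVAs will be marked using the mapping system".

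**The concern.** The Discussion admits that the mapping equipment may influence what is tagged as LAVA, and then divides by the amount tagged. Because the equipment depends on the arm, the divisor can only be measured after assignment, with a tool that differs systematically between the groups. Randomisation balances the true substrate in expectation. It does not balance the measured LAVA area.

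This is a positive claim about a property of the analysis, not a detail left out. It is also the only remedy the paragraph offers for a difference between arms that it concedes. In a 40-patient pilot meant to inform larger trials, a reader told that time per area does not depend on the mapping system may take it as confirming or correcting the raw-time result, when part of the contrast may come from the maps.

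**Working it through.** The article gives no figure for the normalised analysis, so there is none to reproduce. The sample-size calculation plays no part in this point.

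**Inputs from the article**
- Divisor: total LAVA area at baseline, marked on the arm's own system (Substrate mapping; Definition of substrate target).
- Numerator: time to ablate and eliminate all targeted LAVAs (Endpoints). Nearly all tagged areas are targeted, with exceptions, and elimination is checked with the catheter used for the baseline map (Substrate ablation).

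**Assumed quantities** (not in the article)
- k: mapped LAVA area in the PFA arm over that in the RFA arm, for the same true substrate.
- b: how far a mapping difference passes into ablation time, with time scaling as k^b. At b = 0 the extra tagged area adds no time; at b = 1 time rises in full proportion.

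**Step 1: algebra.** With equal true efficiency in both arms, the PFA/RFA ratio of raw times is multiplied by k^b. Dividing by area multiplies it by 1/k, so the normalised ratio is multiplied by k^b / k = k^(b−1). For k ≠ 1 this equals 1 only when b = 1, that is, when time is proportional to mapped area with the same constant in both systems.

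**Step 2: numbers.** Spurious factor on the PFA/RFA ratio, raw → normalised:

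| k | b = 0 | b = 0.5 | b = 1 |
|---|---|---|---|
| 0.8 | 1.00 → 1.25 | 0.89 → 1.12 | 0.80 → 1.00 |
| 1.25 | 1.00 → 0.80 | 1.12 → 0.89 | 1.25 → 1.00 |
| 1.5 | 1.00 → 0.67 | 1.22 → 0.82 | 1.50 → 1.00 |

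For example, at k = 1.25 and b = 0.5: 1.25^0.5 = 1.12 raw, and 1.12 / 1.25 = 0.89 normalised.

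**Step 3: does normalising help?** On the log scale, for b between 0 and 1, the raw bias has size b·|ln k| and the normalised bias (1−b)·|ln k|. They are equal at b = 0.5. Above that, normalising reduces the bias and at b = 1 removes it. Below that, normalising enlarges it.

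**Step 4: effect on a 5% test.** Simulation with equal true efficiency, 20 per arm, 20,000 runs, two-sample t test, log-normal data, and assumed coefficients of variation of 50% for area and 35% for time. Rejection rate, raw / normalised:

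| k | b = 0 | b = 0.5 | b = 1 |
|---|---|---|---|
| 1.25 | 5% / 50% | 8% / 16% | 19% / 5% |
| 1.5 | 5% / 95% | 17% / 43% | 50% / 5% |

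At k = 1 every rate is about 5%. At b = 0.5 the two log-scale biases are equal in size, but the normalised test rejects more often because dividing by area also removes the patient-to-patient variation in area.

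**Step 5: is b = 1 secured by the article?** No. Three of its own rules under Substrate ablation weaken proportionality.
- LAVA areas may be left untreated because of collateral damage, and ablation near metallic devices is to be avoided. Such areas stay in the total-area divisor but add no ablation time. If a share s of the mapped area is spared and time is c(1−s)A, then time per area is c(1−s) and the between-arm ratio carries (1−s_PFA)/(1−s_RFA). This cancels only if the spared shares are equal.
- Further ablation is encouraged for persistent myocardial capture as well as for persistent LAVA. If that time is counted, it need not follow LAVA area.
- Elimination is judged with the arm-specific mapping catheter. A difference between catheters in detecting residual LAVA would change the time without changing the baseline area.

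**The case against.** The strongest reply is that the planned workflow links the two quantities. Nearly every tagged LAVA area is to be ablated, and persistent LAVA is to be treated again. A system that tags more therefore also generates more ablation, so numerator and denominator rise together. At b = 1 the normalised ratio is undistorted, while raw time is off by the full factor k and its test rejects 19% or 50% of the time in the simulation. This stands. A reader might infer that dividing by area necessarily imports the bias it is meant to remove. The article does not support that: normalisation may well improve on raw time.

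The analysis is also a subordinate one. It appears only in the limitations paragraph, not in Table 3 or the statistical section. The suggestion that it is more objective is hedged, the mapping difference is openly disclosed, and only slight differences in targets are expected. The primary test is on raw time and cannot be formally overturned by this analysis. All of this stands and limits the weight of the point.

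Finally, how LAVA area is annotated or centrally reviewed may be set out in the full protocol or analysis plan. The absence of such a procedure from the article is therefore not held against it. What remains is the unconditional statement. None of these arguments rescues it, because the first one is itself an appeal to proportionality, which the article neither states nor justifies.

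**Conclusion.** The claim of independence does not hold as written. The normalised result is independent of the mapping system only if ablation time is proportional to mapped LAVA area with the same constant in both systems.

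Outside that case, with k assumed between 0.8 and 1.5, the spurious factor on the normalised PFA/RFA time ratio runs from 0.67 to 1.25. The range includes 1.00, meaning no distortion. The ends, 0.67 and 1.25, belong to the extreme b = 0, where extra tagged tissue adds no ablation time at all, and should not be quoted as the expected size. Both k and b are assumptions, and neither the direction nor the size of any bias can be learned from the article.

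The point concerns what an additional analysis may be said to show. It does not invalidate that analysis or the primary comparison.

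**What to change.** 1. Delete the statement of independence, or make it conditional. For example: time per unit LAVA area accounts for differences in mapped area only to the extent that ablation time is proportional to mapped area to the same degree in both arms' mapping systems.
2. Label time per area exploratory, and always report it beside raw time and baseline LAVA area by arm, so that a reader can see whether a difference comes from the numerator or the divisor.
3. State that the contrast estimated, in both the raw and the normalised analysis, is the PFA workflow with its mapping system against the RFA workflow with its own.

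Adjustment for baseline LVEF is optional, for precision or for chance imbalance in substrate. It is not a remedy here: a covariate measured before randomisation carries no information on how differently two mapping systems tag the same scar.

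The cost is a few sentences in the analysis plan and the results paper, plus one descriptive table. LAVA area and ablation time are already needed for the planned analysis, so treatment, sample size and data collection do not change.
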